##### AM-PAC “6-Clicks” Functional Mobility

The 6-Clicks is a secondary outcome measure and assesses the difficulty or level of assistance needed for bed mobility, sit-to-stand, supine-to-sit, seated transfers, walking, and ascending stairs; scores are predictive of discharge needs after total knee and hip arthroplasty [36]. The 6-Clicks score is part of standard clinical care and will be recorded from the electronic health record at the 24-hour PT session.

##### Diaphragm Ultrasonography

Ultrasound is an exploratory outcome measure that will be used to calculate diaphragm thickness and thickening fraction during quiet breathing and maximal inspiratory efforts. Ultrasound procedures will follow the methods outlined by Sarwal et al [37].

### Feasibility and Safety Assessments

The electronic health record will be queried to obtain relevant information on patient, surgical, and postoperative information pertaining to the acute hospitalization, including clinical PT documentation of participant demographics, vital signs, dyspnea, functional status (AM-PAC “6-Clicks” functional mobility score), and walking distance at the 24-hour PT session. Feasibility of dIST and aIST is an exploratory aspect that will be assessed using the percentage of projected sessions completed by the participant, the proportion of participants assigned to dIST who are able to complete >75% of prescribed training sessions, and the average change in MIP between the baseline and day-of-surgery assessment points. To monitor PPCs, the study team will record relevant vital signs, requirements for supplemental oxygen, discharge information, and any pulmonary complications or unanticipated health care interventions needed up to 30 days postoperatively.

### Study Oversight

Participants will report levels of pain and dyspnea and undergo assessment of their vital signs before, during, and after study testing. Additionally, participants will also be asked to document their dyspnea during IST sessions and report any unusual symptoms during training. Safety will be monitored through adverse event reporting to the IRB, as well as reporting to an external safety officer. Adverse events will be tracked using a log. Nonserious and serious expected events will be reported biannually to the safety officer and annually to the IRB. Any adverse events determined to be serious, unexpected, and possibly related to study participation will be reported within 5 days to the IRB and within 48 hours to the safety officer and funding source. In addition to safety oversight, the IRB and funding agency will review study progress toward milestones at least annually and may elect to conduct random audits.

### Data Analysis

#### Sample Size Projection

The primary outcome measure is MIP. To project the sample size needed to detect changes in respiratory strength following dIST vs SOC, postoperative changes in MIP were obtained from a controlled, blinded study of IST in cardiac surgery [38]. Relative to baseline, postoperative MIP decreased by an average of 28 (SD 16) in the usual care group but only by 10 (SD 17) in the IST group. These data, along with similar publications of preoperative IST, demonstrate a moderate to large potential effect size to detect changes in MIP [22,24,26]. With a total of 36 participants (12 per group), a mixed-effects test could detect a 3×3 group-time interaction effect for training (partial η²=0.06, effect size (f)=0.253, α=0.05, 1−β=0.83).

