## Abstract

**Background:**

Total joint arthroplasty (TJA) is among the most common elective surgeries performed in the United States, and recent advances in perioperative care have shortened hospital stays and streamlined recovery. Yet, even brief periods of mechanical ventilation and anesthesia measurably weaken respiratory muscle function in the early postoperative period. Preoperative inspiratory strength training (IST) has been shown to reduce postoperative pulmonary complications in patients undergoing major cardiothoracic surgery, but whether these benefits extend to shorter procedures such as TJA, where hospital stays are already brief, remains unknown.

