### Participant Recruitment and Screening

Individuals with physician approval for elective joint replacement surgery who are interested in research participation will be referred to the study team by the Department of Orthopedics. We will enroll up to 60 participants. This includes 30% (18/60) participants who participated in nonrandomized, proof-of-principle pilot work for the purpose of estimating the sample size for the randomized study. Up to 70% (42/60) additional participants will be randomized, with the goal of completing procedures in 60% (36/60) randomized participants. The inclusion criteria are outlined in Textbox 1. Patients who meet the eligibility criteria and agree to participate in the study will sign a University of Florida Institutional Review Board (IRB)–approved informed consent form. The study coordinators will screen patients according to the inclusion and exclusion criteria via participant interview and medical record review.

Textbox 1.Inclusion and exclusion criteria for study participation.

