#### SOC

The SOC group will serve as the control group and will receive usual preoperative, surgical, and postoperative care. This includes the preoperative TJA class sponsored by the Department of Orthopedics, preoperative lower extremity strengthening home exercises, provision of an assistive device, and counseling for smokers to quit smoking preoperatively.

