The primary outcome of this trial is MIP, a clinical estimate of strength. However, additional secondary measures were included to investigate the effects of the interventions on early postoperative activity-based measures such as coughing force, walking distance, and functional mobility, along with patient-reported dyspnea. Postoperative walking and functional mobility are important functional limitations following TJA that influence the timing of disposition and postacute rehabilitation needs [40]. Although the projected effect size of preoperative IST appears robust for impairment-level outcomes, this study will also provide early indication of its ability to carry over to functional activities and participation-level recovery. As preoperative 6MWD can predict functional ambulation after total joint surgeries [41], the statistical plan will explore preoperative walking distance as a covariate.

As a first preliminary study in TJA, some aspects of the study design remain limited. The sample size was projected from published work in cardiac surgery to detect changes in MIP between dIST and no preoperative exercise. Although we anticipate gaining valuable feasibility information regarding completion of aIST in the acute preoperative setting, we may lack the power to comprehensively distinguish which preoperative training approach (dIST or a single aIST session) can more effectively retain postoperative MIP and functional mobility. Postoperative walking and functional mobility at 24 hours can be influenced by a multitude of factors beyond respiratory strength and may include variations in pain management and pain perception, the ability to participate in same-day therapy, and lack of sleep, nutrition, or hydration. Blinded evaluators will plan for premedication with nursing before the planned 24-hour PT session and ensure that the timing does not interfere with meals. Participants randomized to SOC did not receive a respiratory trainer or training diary or undergo weekly check-ins, and the absence of a sham or attentional control group could inadvertently introduce expectation bias. Even in higher-risk patients, there may be few PPCs in the 30-day period following TJA. However, monitoring complications will enable us to further explore the prevalence of postoperative pulmonary issues in this cohort. Surgeons and study evaluators will be blinded to group assignment, but patients and other study staff will, by necessity, know the allocation.

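### The stated power of 0.83 belongs to an omnibus 3×3 interaction. The dIST versus SOC contrast named in the sizing has about 0.72 to 0.75 on the article's own cardiac-surgery inputs, and the pilot said to have been run for sizing does not appear.

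*Protocol article*

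**What the plan says.** The Sample Size Projection section names dIST versus SOC as the comparison to be sized. Its numerical input is from cardiac surgery: "postoperative changes in MIP were obtained from a controlled, blinded study of IST in cardiac surgery". The result reported from that study, as change from the baseline value, is: "postoperative MIP decreased by an average of 28 (SD 16) in the usual care group but only by 10 (SD 17) in the IST group". The section adds: "These data, along with similar publications of preoperative IST, demonstrate a moderate to large potential effect size to detect changes in MIP". It then gives power 0.83 at α=0.05 for a 3×3 group-by-time interaction with partial η²=0.06 (f=0.253) and 36 participants, 12 per group. No within-person correlation is given, and no step leads from 28 versus 10 to f.

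Four other places bear on this:

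- Participant Recruitment and Screening counts 18 of the 60 participants as having joined "nonrandomized, proof-of-principle pilot work for the purpose of estimating the sample size for the randomized study".
- The SOC section defines the comparator: "The SOC group will serve as the control group and will receive usual preoperative, surgical, and postoperative care". Here that means usual arthroplasty care.
- The Abstract says that "whether these benefits extend to shorter procedures such as TJA, where hospital stays are already brief, remains unknown".
- The Discussion lists the source as a limitation: "The sample size was projected from published work in cardiac surgery to detect changes in MIP between dIST and no preoperative exercise". It also describes the projected effect size for impairment-level outcomes as seemingly robust.

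**The concern.** Two things do not fit together.

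First, the projection opens with a two-arm question and closes with the power of a different, omnibus test. A reader will take 0.83 as the chance of detecting dIST against SOC. If the power for that contrast is lower, a non-significant result is more likely than the article implies and could be over-read as evidence against training.

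Second, the article gives two accounts of how the sample size was reached. One says that a pilot was run for that purpose. The other says that the number came from cardiac surgery, a setting from which the article says transfer is unknown. The projection contains no pilot mean, SD or correlation.

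**Working it through.** **Inputs.** From Sample Size Projection: mean falls 28 (SD 16) and 10 (SD 17), 12 per group, 36 in total, three groups, three times, f=0.253, α=0.05. Assumed, because not stated: within-person correlation ρ and sphericity.

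**1. The plan's own figure.** f = √(0.06/0.94) = 0.253. For the within-between interaction, λ = f²·N·m/(1−ρ), with df (3−1)(3−1) = 4 and (36−3)(3−1) = 66.

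- At ρ=0.5: λ = 0.253² × 36 × 3 / 0.5 = 13.83, power 0.833. The stated 0.83 is reproduced.
- The result depends on ρ: 0.67 at ρ=0.3, 0.75 at 0.4, 0.91 at 0.6.

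**2. The named contrast on the cardiac inputs.**

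- Difference: 28 − 10 = 18.
- Pooled SD: √((16² + 17²)/2) = 16.5.
- d = 18/16.5 = 1.09.
- Noncentrality: 1.09 × √(12/2) = 2.67.
- Two-sided 0.05, two-sample t (22 df): power 0.72.
- Same noncentrality with the pooled error df of the three-group model (66): power 0.75.
- If the first Holm step tests at 0.025 (an assumed family of two), the 22-df figure is 0.61. The article does not give the size of the Holm family, so this is only an illustration.

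**3. Detectable difference.** Power 0.80 at 12 per group needs d=1.20 (22 df), so 1.197 × 16.5 = 19.8 units. With 66 df it is 1.161 × 16.5 = 19.2. Either is larger than the 18 in the cited study.

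**4. Is f=0.253 a discounted cardiac effect?** Assume ρ=0.5, so that the SD at a single visit equals the SD of change, 16.5. Let one arm differ by δ at one visit. The interaction effect is then f = (2/9)·δ/16.5.

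- δ=18 gives f=0.242, power 0.80.
- f=0.253 requires δ = 0.253 × 16.5 × 4.5 ≈ 18.8.
- If aIST lies midway between the other two arms at the postoperative visit, δ=18 gives f=0.210, power 0.66.

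Under these patterns f is no smaller than what the cardiac result implies. Other correlations or patterns of means would change this, and the article does not say which it used.

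**5. How the contrast power moves.** Two-sample t, 12 per group, two-sided 0.05. The differences and SDs are assumptions, apart from the pair 18 and 16.5.

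| Difference | SD 12 | SD 16.5 | SD 20 |
|---|---|---|---|
| 9 | 0.42 | 0.25 | 0.18 |
| 12 | 0.65 | 0.40 | 0.29 |
| 15 | 0.83 | 0.57 | 0.42 |
| 18 | 0.94 | 0.72 | 0.56 |

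The SD matters as much as the difference, and the article gives neither for arthroplasty.

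**The case against.** The arithmetic of 0.83 is right. The sentence is conditional (this test could detect this f), and the text never claims that f was computed from 28 versus 10. Borrowing an effect from the nearest surgical field is ordinary for a first study, and the Discussion discloses the source and calls the study preliminary. With 31 participants enrolled by May 2026, restating power changes nothing in the conduct of the trial. All of that stands, and it keeps the point modest. However, the one power shortfall that the Discussion admits concerns dIST against aIST. It does not qualify dIST against SOC, and it does not mention the pilot.

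A reader might go further and infer that arthroplasty patients lose less MIP than cardiac patients, that the SOC fall caps what training can prevent, and that true power is therefore well below 0.72. The documents do not support this:

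- The 28 and 10 are changes from baseline, so the 18-unit gap may include strength gained before surgery, which is what aim 1 expects. The surgical fall does not limit such a gain.
- The SD need not stay at 16.5 if the falls are smaller. With a difference of 9, power is 0.25 at SD 16.5 but 0.72 at SD 8.25.
- The introduction describes shorter procedures and brief ventilation, which makes a smaller fall plausible, but it gives no arthroplasty MIP figure.

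**Conclusion.** The point holds in a limited form. The 0.83 is a correct figure for a test other than the comparison that the section says it is sizing, and it rests on an unstated correlation. On the article's own inputs, dIST versus SOC has power of about 0.72 to 0.75 before Holm, roughly 8 to 11 percentage points below the stated value, with about 20 units detectable at 80% power. This assumes normal changes, 12 completers per group and the cardiac difference and SD at face value, with that change from baseline treated as the contrast of interest.

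Separately, the recruitment section conflicts with the Sample Size Projection and the Discussion on whether the pilot or cardiac surgery supplied the sample size. Whether power in arthroplasty is lower or higher than these figures cannot be determined from the documents.

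**What to change.** Leave the sample size unchanged and correct the text:

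1. Make Participant Recruitment and Screening agree with the Sample Size Projection and the Discussion on what the 18-person pilot was used for.
2. In the Sample Size Projection, label 0.83 as the power of the omnibus 3×3 interaction, conditional on f=0.253 and on the assumed correlation, and state that correlation. Add the power (0.72 to 0.75 before Holm) and the detectable difference (about 20 units) for dIST versus SOC at 12 per group.
3. Show that power over a range of differences and SDs, as in the table above. Use the pilot SD and correlation where available. Do not replace the effect size with an estimate from 18 nonrandomized participants, which would be imprecise and open to bias.
4. In the Discussion, qualify the description of the projected effect size as robust.

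The cost is a few hours of analysis on existing data and some rewording, with no added participants or procedures. The downside is that the stated power becomes less favourable.

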#### Statistical Analysis

To test whether dIST or even a single aIST session can accelerate postoperative respiratory and functional recovery, the primary analysis will compare between-group changes using a mixed-effects model to account for within-subject correlation in repeated measurements. Fixed main effects will include intervention and time; the participant will be included as the random effect. If baseline measures differ between groups, an analysis of covariance (ANCOVA) will be used. The primary analyses will be (1) change in MIP for dIST (vs other groups) from baseline to the preoperative assessment and (2) change in MIP from the preoperative assessment to the postoperative assessment for dIST and aIST (vs SOC). Holm adjustments will be applied for multiple comparisons.

Feasibility will be characterized by the percentage of completed dIST sessions, diary completion, and attrition rate. These will be reported as descriptive variables. The prevalence of PPCs will be compared between groups using chi-square or Fisher exact tests, as appropriate.

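### The stated power of 0.83 belongs to an unadjusted group-by-time interaction test, not to the Holm-adjusted MIP comparisons that the plan names as primary

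*Protocol article*

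**What the plan says.** In the Protocol article, Sample Size Projection, the sample is "With a total of 36 participants (12 per group"). The claim is that "a mixed-effects test could detect a 3×3 group-time interaction effect for training", with a partial η² of 0.06 and "effect size (f)=0.253, α=0.05, 1−β=0.83". The effect behind it is taken from a cardiac surgery study, in which "postoperative MIP decreased by an average of 28 (SD 16) in the usual care group but only by 10 (SD 17) in the IST group", both measured relative to baseline.

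The Statistical Analysis section then defines two primary analyses. The first is "change in MIP for dIST (vs other groups) from baseline to the preoperative assessment". The second is "change in MIP from the preoperative assessment to the postoperative assessment for dIST and aIST (vs SOC"). It adds that "Holm adjustments will be applied for multiple comparisons".

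The sample size section mentions neither Holm's method nor these comparisons. The Discussion concedes limited power only for telling dIST from aIST, and describes the projected effect on impairment-level outcomes as robust.

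**The concern.** The test that was powered is not the test that decides the trial. This shows in two ways.

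- **Different test.** The interaction test asks whether there is any departure from parallel profiles across three groups and three times (4 degrees of freedom). The primary analyses are contrasts between particular groups over particular intervals. An interaction effect size does not fix the power of any one contrast.
- **Different threshold.** Power is quoted at 0.05. Read plainly, the primary analyses contain four comparisons: dIST vs aIST and dIST vs SOC before surgery, then dIST vs SOC and aIST vs SOC across surgery. There are three if the other groups are pooled in the first analysis. Holm's method tests the smallest p-value at 0.0125 or 0.0167 respectively.

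A reader will take 0.83 as the chance of confirming the main claims. If the real chance is nearer one half, a non-significant primary comparison says much less about absence of effect than the stated power suggests.

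**Working it through.** **1. Reproduce the plan's figure.**

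Inputs from Sample Size Projection: N = 36, 3 groups, m = 3 times, partial η² = 0.06, f = 0.253, α = 0.05. The effect sizes agree: √(0.06/0.94) = 0.2526. The article gives no within-subject correlation ρ, so ρ = 0.5 is assumed, with sphericity.

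- λ = f² × N × m/(1 − ρ) = 0.253² × 36 × 3/0.5 = 13.83
- df = (3 − 1)(3 − 1) = 4 and (36 − 3)(3 − 1) = 66
- Power of the F test at 0.05 = **0.833**

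This matches 0.83. The result depends on ρ: the same formula gives 0.50 at ρ = 0 and 0.998 at ρ = 0.8. The stated figure is therefore an unadjusted 4-df interaction test.

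**2. Power of a pairwise comparison on the cited effect.**

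Inputs from the same section: mean falls of 28 and 10, SDs 16 and 17, 12 per arm.

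- Difference = 28 − 10 = 18
- Pooled SD = √((16² + 17²)/2) = √272.5 = 16.51
- d = 18/16.51 = 1.09
- Noncentrality = d × √(12/2) = 1.09 × 2.449 = 2.67

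Power from the two-sided noncentral t distribution. The first column uses the two compared groups only (df 22). The second uses a residual with 66 df, as a mixed model might.

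| Level | Where it arises | df 22 | df 66 |
|---|---|---|---|
| 0.05 | unadjusted | 0.72 | 0.75 |
| 0.025 | first step, two comparisons | 0.61 | 0.65 |
| 0.0167 | first step, three comparisons | 0.54 | 0.59 |
| 0.0125 | first step, four comparisons | 0.49 | 0.54 |

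**3. dIST against both other groups pooled (12 vs 24).**

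The same difference and SD are assumed.

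- Noncentrality = 1.09 × √(12 × 24/36) = 1.09 × 2.828 = 3.08
- Power at 0.05 = 0.85 (df 33) to 0.86 (df 66)
- Power at 0.0167 (three comparisons) = **0.71** to 0.73

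**4. How much is due to Holm.**

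For a pairwise comparison (df 22), power falls from 0.83 to 0.72 before any adjustment, because the test differs. It falls from 0.72 to 0.49 with the first-step adjustment for four comparisons. Both parts matter.

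**5. What f = 0.253 alone implies.**

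With ρ = 0.5 and df 66, contrast power depends on the pattern of means:

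- If only dIST gains before surgery and keeps the gain, dIST vs SOC before surgery has power 0.59 at 0.0125.
- If effects are spread evenly over groups and intervals, each of the four pairwise comparisons has 0.22 at 0.0125.
- If only dIST gains and it loses half by 24 hours, the pooled dIST contrast before surgery has 0.89 at 0.0167.

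**The case against.** Several points on the other side stand.

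- **The interaction calculation is internally consistent.** A level of 0.05 is right for one omnibus test, and the 0.83 is correct for what it describes. The fault lies in what it is offered to support.
- **A reader might infer that no primary comparison can reach 0.83.** The documents do not support that. The effect size f does not fix the pattern of means, and the last pattern above gives a pooled contrast with power 0.89 at its Holm first step.
- **A reader might blame Holm alone, or replace 0.83 with about 0.66.** The latter is the interaction test run at 0.0125. The plan applies Holm to comparisons, so that figure describes no test in the plan, and it exceeds the pairwise figure on the cited effect.
- **The cited effect fits neither primary interval.** It runs from baseline to after surgery, whereas the primary analyses split that span at the preoperative assessment. The pairwise figures are illustrative.
- **First-step thresholds are Holm's strictest.** Later steps are looser, so these figures are a lower bound. The gap is small: simulating the pattern in which dIST alone gains and keeps the gain gave 0.59, against about 0.57 to 0.59 at the first step.
- **A reader might infer an inflated false-positive rate.** Under the complete null, simulated familywise error is about 4.5% with one Holm family of four and 8.4% with two families of two. The article does not say that it splits the family. One family is the natural reading, and its exact membership is detail for an analysis plan.

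The mismatch remains. An analysis plan could define the Holm family, but it could not turn the published 0.83 into the power of the comparisons named as primary.

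**Conclusion.** The concern holds in this form: 0.83 is the power of an unadjusted 4-df interaction test, and the article gives no power for the Holm-adjusted comparisons it calls primary.

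On the only difference and SDs it cites, pairwise power is about 0.5 at the first step for four comparisons (0.49 to 0.54 depending on degrees of freedom), and about 0.61 to 0.65 if the family has two. A pooled dIST comparison in a family of three has about 0.71 to 0.73.

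These figures assume 12 completers per arm, two-sided tests, and that the cited change and SDs carry over to the primary intervals. They show how far the stated power can be from that of the primary comparisons; they are not exact values for them. The trial is still enrolling and results are expected in 2027, so the statement can be corrected before analysis.

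**What to change.** In Sample Size Projection:

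- State that 0.83 applies only to the unadjusted 3×3 interaction test, and give the within-subject correlation it assumes.
- Add the power of the primary pairwise comparisons at their Holm level, with the assumed difference, SD and interval shown. On the cited effect this is about 0.5 at 0.0125 for four comparisons, and about 0.6 at 0.025 if the family has two.

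In Statistical Analysis:

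- Confirm that Holm's method covers all comparisons in both primary analyses as one family, and say whether the other groups are pooled in the first analysis, since that decides between three and four.

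The cost is a few sentences and a less favourable power statement. No extra patients are needed.
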